## Abstract

**Introduction:**

It is unclear whether routine testing of women for group B streptococcus (GBS) colonisation either in late pregnancy or during labour reduces early-onset neonatal sepsis, compared with a risk factor-based strategy.

**Methods and analysis:**

Cluster randomised trial.

**Sites and participants:**

320 000 women from up to 80 hospital maternity units.

**Strategies:**

Sites will be randomised 1:1 to a routine testing strategy or the risk factor-based strategy, using a web-based minimisation algorithm. A second-level randomisation allocates routine testing sites to either antenatal enriched culture medium testing or intrapartum rapid testing. Intrapartum antibiotic prophylaxis will be offered if a test is positive for GBS, or if a maternal risk factor for early-onset GBS infection in her baby is identified before or during labour. Economic and acceptability evaluations will be embedded within the trial design.

**Outcomes:**

The primary outcome is all-cause early (<7 days of birth) neonatal sepsis, defined as either a positive blood/cerebrospinal fluid culture, early neonatal death from infection or a negative/unknown culture status with ≥3 agreed clinical signs or symptoms, who receive intravenous antibiotics ≥5 days. All women giving birth ≥24 weeks’ gestation, regardless of mode of birth, and all her babies will be included in the dataset. Cost-effectiveness will be expressed in terms of incremental cost per case of early neonatal sepsis avoided and incremental cost per quality-adjusted life-year associated with each strategy.

**Ethics and dissemination:**

The trial received a favourable opinion from Derby Research Ethics Committee on 16 September 2019 (19/EM/0253). The allocated testing strategy will be adopted as standard clinical practice by the site. Women in the routine testing sites will give verbal consent for the test. The trial will use routinely collected data retrieved from National Health Service databases, supplemented with limited participant-level collection of process outcomes. Individual written consent will not be sought. The trial results, and parallel economic, qualitative, implementation and methodological results, will be published in the journal Health Technology Assessment.

**Trial registration number:**

ISRCTN49639731.

STRENGTHS AND LIMITATIONS OF THIS STUDYThis study is a cluster randomised trial to determine the clinical and cost effectiveness of routine testing for group B streptococcus in pregnancy.320 000 participants will be adequately powered to detect a small but meaningful difference in early-onset neonatal sepsis.The study is not designed to detect a difference in early-onset neonatal sepsis between the two testing strategies but will provide information on acceptability and ease of implementation of the two testing strategies.

We use the term ‘women’ throughout to refer to those who are pregnant and give birth. We acknowledge that not all people who are pregnant and give birth identify as women, and it is important that evidence-based care for maternity, perinatal and postnatal health is inclusive.^1^

## Introduction

 One in four pregnant women in the UK carries group B streptococcus (GBS) in the gut and genital tract. Approximately 50% of babies whose mothers carry GBS will also be colonised, and of those, 3% will develop early-onset GBS (EOGBS) infection.^2^ EOGBS infection (occurring <7 days after birth) is caused by GBS bacteria ascending from the maternal genital tract during pregnancy (usually in the presence of ruptured membranes, although it can occur with intact membranes) or labour.^3^ EOGBS infections tend to manifest as pneumonia and sepsis and affect 1 per 1750 births in the UK (517 babies per year).^4^ GBS is the most common proven cause of early-onset infection (accounting for 40% of all isolates in culture positive cases) in the UK.^3^ One study has estimated that in the UK EOGBS infection causes more than 40 neonatal deaths and around 25 cases of long-term disability every year.^5^ Mortality is around 5%–10%, but higher among preterm babies (23%).^6 7^

Epidemiological studies have suggested that various factors (preterm labour, GBS colonisation or bacteriuria in the current pregnancy, a previous baby with GBS infection, maternal fever during labour) present at the time of birth are associated with the baby having an increased risk of developing GBS infection (presenting as either an early or late onset infection). However, a systematic review estimated that 65% of deliveries had no recognised maternal risk factors for GBS infection.^8^

Giving intrapartum antibiotic prophylaxis (IAP) to mothers who are known to carry GBS has been shown to reduce EOGBS infection.^9^ However, antibiotics may cause short-term complications for the mother (anaphylaxis, medicalisation of labour) or baby (effects on gut microbiome), may have long-term complications for the mother or baby^10^ and may increase antimicrobial resistance both for the individual and the wider population.

The current UK strategy involves identifying maternal risk factors for their baby developing EOGBS infection and then offering these ‘higher risk groups’ IAP.^11^ Additionally, women where GBS detected in a previous pregnancy are offered the option of bacteriological testing in late pregnancy and IAP if GBS-positive, or IAP without testing.

Universal testing for GBS is undertaken in many developed countries and has been attributed to the reduction in EOGBS infection. In the USA, the incidence of EOGBS infection per 1000 live births fell from 0.47 in 1999–2001 to 0.34 in 2003–2005 to 0.25 in 2010.^12^ The risk of EOGBS infection is significantly lower among infants of mothers undergoing universal testing than those who undergo a risk factor-based approach to prevention, with an adjusted relative risk (RR) of 0.46 (95% CI 0.36 to 0.60).^13^ The corresponding incidence in 2014–2015^4^ in the UK is 0.57/1000 births, a significant increase since previous surveillance undertaken in 2000 (0.48/1000)^7^ despite the introduction of a risk factor-based approach in 2003.^11^

The UK National Screening Committee (NSC) recommends ‘not to screen for maternal GBS carriage in the general population’ due to the absence of randomised trial data on either its effectiveness or cost-effectiveness.^14^ Testing would result in tens of thousands of women being offered and having IAP administered unnecessarily, while the long-term effects remain unknown. The key issue, when testing at 35–37 weeks of gestation was considered, was the lack of randomised trial data, evidence of efficacy and the accuracy of this antenatal testing as an indication of neonatal risk status at delivery.^15^ The NSC review recommended a randomised controlled trial, noting, however, that the positive predictive power of an antenatal testing policy for the outcome of a baby with EOGBS infection would be very low.

The enriched culture media (ECM) microbiological test is recognised as the international ‘gold standard’ for detecting GBS. It is highly sensitive, but maternal colonisation can alter through pregnancy.^16^ It takes at least 48 hours to produce a result and is usually offered at 35–37 weeks’ gestation, so misses most preterm births. Intrapartum rapid molecular tests have the potential to enable more accurately targeted IAP with current colonisation status, but the result may not be available in time for fast labours, there is no time for sensitivity testing for those allergic to penicillin, less time for the pregnant woman to be counselled and consider options if positive and it is more expensive than ECM.

### Trial objectives and design

#### Objectives

To determine whether routine testing of women for GBS colonisation either in late pregnancy or during labour reduces the occurrence of early-onset neonatal sepsis, compared with the current risk factor-based strategy.

To determine the cost-effectiveness, acceptability and ease of implementation of testing.

To compare two routine testing strategies (ECM and rapid test), to determine whether the proportion of women providing a sample for testing differs, whether either or both methods provide a timely result and the impact on neonatal admission.

#### Design

A multicentre prospective two-group parallel cluster randomised trial with embedded economic evaluation and qualitative study within a trial.

## Methods and analysis

### Setting and site level eligibility

Maternity hospitals (obstetric units (OU) and alongside midwifery units (AMUs)) if able to accept women requiring IAP are eligible to participate if, with training and support, they are able to implement the antenatal ECM or intrapartum rapid testing strategies. A list of 67 participating hospital trusts and health boards making up 71 sites in England and Wales is provided in online supplemental file 1.

One National Health Service (NHS) Trust may contain several maternity units. Each unit is then considered as an individual cluster site if the routine data sources could discriminate between the maternity units within the Trust and each maternity unit was able to maintain its allocated group.

The contracted microbiology laboratories providing services to the sites had to be prepared to use Public Health England (PHE, now UK Health Security Agency) Standard for Microbiological Investigations (SMI) B58 for the ECM testing for GBS for the duration of the trial. The PHE SMI B58 is the national guidance on the UK Standards for Microbiology Investigations for detection of carriage of GBS.^17^ Participating sites also had to be prepared to host a Cepheid GeneXpert system in a location convenient to the delivery suite.

Randomisation is at the site level to avoid any risk of contamination. Eligible sites are randomised on a 1:1 ratio to a routine testing strategy or to the risk factor-based strategy, using a minimisation algorithm with a random element.

Minimisation variables were overall number of births per year (<4000, 4000–4999 and ≥5000), according to national data for preceding year; neonatal unit level of care tier associated with the participating maternity unit (special care unit, local neonatal unit or neonatal intensive care unit)^18^ and presence of AMU.

There was a further second-level randomisation of the routine testing sites to either antepartum ECM testing or intrapartum rapid testing, restricted to achieve balance.

Withdrawal of sites after randomisation is avoided, if at all possible, in order to reduce bias.

### Individual-level eligibility

There are two levels of eligibility for individual women:

Testing level—eligibility to be offered an ECM or rapid test.

Dataset level—eligibility to be included in the dataset for analysis, regardless of whether test performed.

There is no exclusion based on the age of women or multiple births.

### Testing policy in each type of site

#### Inclusion criteria

In ECM sites:All women attending an antenatal clinic at ≥35 weeks of gestation without a planned delivery date.3–5 weeks prior to a planned induction date, or planned elective caesarean date prior to 40 weeks’ gestation.In rapid test sites:All women who experience labour or prelabour rupture of membranes at ≥37 weeks’ gestation.Women planning a home birth or in a free-standing midwifery unit (FMU) (which is not able to offer IAP) can be offered an antenatal rapid test which will be processed on the maternity unit/labour suite at ≥35 weeks gestation.In risk factor sites, all pregnant women at ≥24 weeks’ gestation. All women with risk factors should be reviewed for IAP/bacteriological testing in line with the Royal College of Obstetricians and Gynaecologists (RCOG) Greentop guidelines, detailed below.^11^

#### Exclusion criteria

Women who do not provide verbal consent to have a swab.Women who have had a previous baby with GBS infection (early or late onset) and who want IAP. However, these women can still be offered a test and can choose to have IAP regardless of the result.Women in preterm labour (suspected, diagnosed, established), at ≤37 weeks gestation should be offered IAP routinely.In rapid test sites, women who have been admitted for a planned elective caesarean birth. (If women labour spontaneously at ≥37 weeks and plan not to proceed with the elective caesarean, they should then be offered a test.)In rapid test sites, women who require an emergency caesarean but who have intact membranes and are not in labour.Known congenital anomaly incompatible with survival at birth, of a singleton or all multiple fetuses.Known prelabour intrauterine death in the current pregnancy, of a singleton or all multiple fetuses.

Two categories of women should be offered IAP regardless of the result of the GBS test:

Women who have previously had a baby with GBS disease should be offered a test but can choose to have IAP regardless of the result.Women with true GBS bacteriuria that has been treated with antibiotics earlier in the current pregnancy.

In all other cases, where the most recent antenatal ECM or intrapartum rapid test result differs from GBS status identified earlier in the pregnancy (such as detected as an incidental finding on a routine high or low vaginal swab), the later GBS status result should supersede the earlier one. The most recent GBS status should be used to determine the offer of, and administration of, IAP.

#### Dataset level criteria

In all units, all women giving birth ≥24 weeks’ gestation within their site’s study period, regardless of mode of birth, and all her babies will be included in the dataset unless they exercise their right to withdraw consent to use routine data, through the NHS data-opt out (or devolved nation equivalent).

Women who experience an intrapartum stillbirth will be included as they may have had testing for GBS, and GBS may be implicated in the aetiology of their stillbirth. If the stillbirth was antepartum, the woman will be included as she may have had antenatal testing for GBS prior to in utero death. However, women whose fetus (all fetuses in the case of multiples) had known congenital anomaly incompatible with survival at birth are excluded.

### Strategies to be compared

The routine testing strategies use antenatal ECM testing or intrapartum rapid testing using the Cepheid GeneXpert system, with IAP offered if the test is positive for GBS presence in the sample taken. The control strategy is to offer IAP if a maternal risk factor for EOGBS infection in her baby is identified before or during labour. Brief details of testing strategies are given in figure 1.

**Figure 1 F1:**
[figure not shown]
Overview flow chart of testing groups and risk factor groups. ECM, enriched culture media; GBS, group B streptococcus; IAP, intrapartum antibiotic prophylaxis; PIS, patient information sheet.

Blinding of women and healthcare professionals is not possible due to the nature of the strategies.

#### Antenatal ECM testing group

Sites randomised to ECM testing will obtain vaginal-rectal swabs from women at ≥35 weeks of gestation for those without a planned birth date (or 3–5 weeks prior to the planned birth date). If a vaginal-rectal swab is not collected in this time window, ECM testing should still be offered, providing a result can practically be achieved and communicated back to the clinical team and/or the woman in advance of the onset of labour.

The test is discussed with and offered to the woman. If she consents to testing, swabs will be obtained by a suitably trained member of the woman’s care team, or the woman may self-swab. The swab can be obtained at antenatal clinics, visits to hospital or in the community. All positive and negative results should be recorded and communicated to the women and clinical staff as per usual local procedures. If the results are not available when the woman goes into labour, risk factor-based guidance should be undertaken in regard to the offering and administration of IAP. The GBS3 ECM antenatal swab result should supersede any GBS result that has been obtained at an earlier gestation during the pregnancy.

The testing protocol is described in online supplemental appendix 2A. ECM testing will follow PHE Standards for Microbiology Investigation B58 and ID4(4) for GBS.^17 19^

#### Intrapartum rapid test sites

Sites randomised to rapid testing will collect vaginal-rectal swabs from women at ≥37 weeks’ gestation if they are in labour (latent or established) or about to be induced. The test is discussed with and offered to the woman. If she consents to testing, swabs are obtained by a suitably trained member of the woman’s care team, ideally before any vaginal examination (if one is to be performed). The testing protocol is described in online supplemental appendix 2B.

If the GBS test is positive, the woman should be informed and offered IAP. The swab should be offered up to the point of birth (sites were advised to use their clinical judgement, and if they did not feel they would have the results of the test in time to give IAP prior to birth, to revert to a risk factor-based approach).

#### Risk factor-based group (usual care)

Sites randomised to the risk factor-based screening and treatment approach will continue to use their current local guidelines which should be based on the RCOG Greentop Guideline 36.^11^ These state that women with the following risk factors for their baby developing EOGBS infection should be offered IAP:

Having a previous baby with GBS infection.

Discovery of maternal GBS carriage during pregnancy.

Preterm labour.

Suspected maternal intrapartum infection, including suspected chorioamnionitis.

Intrapartum fever.

Women who are known to have been colonised with GBS in a previous pregnancy should be offered the options of IAP or ECM testing in late pregnancy with the offer of IAP if GBS is detected. The risk of colonisation in subsequent pregnancies described in the RCOG guidelines should be discussed with the woman.

#### IAP and neonatal management

If a test is positive and the baby is born prior to the woman receiving IAP, neonatal management should be in line with National Institute for Health and Care Excellence (NICE)^20^ and the RCOG guidelines,^11^ covering both all cause and GBS specific infection. Monitoring of the infant and the decision whether to give neonatal antibiotics will be down to clinical judgement and the NICE guidelines.^20^

### Outcomes

#### Primary outcome

All-cause early neonatal sepsis is defined as starting at <7 days of birth. Cases will be identified from national data sources, a sample of which will be reviewed by a blinded adjudication panel (online supplemental appendix 3). Early neonatal sepsis is defined as:

A positive culture of a pathogenic bacteria from blood or cerebrospinal fluid (CSF) taken at <7 days of birth.Death <7 days if infection or sepsis was recorded on the death certificate.Negative/unknown culture status with ≥3 agreed clinical signs or symptoms (see list below), for which intravenous antibiotics are given for ≥5 days, starting within 7 days of birth. If the infant was discharged or transferred prior to the completion of 5 days of intravenous antibiotics, the infant would still be classed as having sepsis if the intention was to treat for 5 or more days.

The following symptoms and signs are considered international standards for neonatal infection up to 28 days from birth and for babies born at all gestations and are level 2 of the Global Alignment on Immunisation safety Assessment in pregnancy consortium (GAIA case definition^21^) but with additional clarification derived from Modi *et al*’s case definition^22^ where the GAIA definition appeared ambiguous.

The following acute-onset clinical or laboratory features will be used as part of the definition of clinically suspected neonatal infection, if the blood and CSF cultures are negative/unknown and intravenous antibiotics are given for ≥5 days, starting within 7 days of birth:

Increase in oxygen requirement or increase in ventilatory support or new or an increase in frequency of episodes of apnoea.Increase in frequency of episodes of bradycardia or hypotension (needing inotrope support or other intervention).Temperature ≥37.5°C or <35.5°C.Enteral feeds intolerance or abdominal distension.*Reduced urine output to <1 mL/kg/hour.*Impaired peripheral perfusion (capillary refill time >3 s or skin mottling or core-peripheral temperature gap >2°C).Irritability or lethargy or hypotonia (clinician-defined).*Serum C reactive protein levels >15 mg/L or procalcitonin ≥2 mg/mL.*White cells count 20×10^9^ cells/L or platelet count <100×10^9^/L.Glucose intolerance (blood) glucose (<2.2 mmol/L or >10 mmol/L) or metabolic acidosis (base excess <−10 mmol/L or lactate >2 mmol/L).

Note, signs or symptoms marked with an asterisk* may not be able to be identified from some routine sources.

An adjudication panel of UK consultant neonatologists will be convened to review the individual-level data of a sample of babies with clinically suspected sepsis. Two experts, masked to the location of birth and the neonatal unit, will review each case, state their individual opinion regarding the diagnosis of sepsis, and if not unanimous, a third expert will be involved to help reach a consensus. The adjudication panel will also review the individual-level data of babies who die during the intrapartum period, or when the timing of intrauterine death was unclear, to determine whether sepsis was the primary cause of death. Full details of the adjudication panel process will be included in a separate blinded endpoint Adjudication Committee Protocol (online supplemental appendix 3).

#### Secondary clinical outcomes

With the exception of maternal intrapartum anaphylaxis and systemic infection, all neonatal and maternal outcomes will be collected from routine data sources.

#### Neonatal

Birth weight.Perinatal mortality (a stillbirth or early neonatal death, <7 days).Extended perinatal mortality (a stillbirth or neonatal death, <28 days).Baby death before discharge5 min Apgar score.Fetal acidaemia, defined as cord arterial pH<7.05.Gestational age at birth.Admission for neonatal specialist care (length of stay, level of care).Seizures.Abnormal neurological signs (hypotonia or abnormal level of consciousness) at >24 hours of age.Late onset culture-positive (blood or CSF taken from 7 days to ≤28 days of birth) neonatal sepsis including clearly pathogenic organisms and excluding skin organisms (eg, coagulase-negative staphylococci).

#### Maternal

Mode of onset of labour.Mode of birth.Duration of time from ruptured membranes to delivery.Duration of hospital stay.Change of intended location of childbirth.Maternal intrapartum anaphylaxis due to IAP.In a subset of participants for whom detailed data is collected, systemic infection confirmed with a positive blood culture or suspected maternal sepsis, from onset of labour to 42 days after birth.Maternal death, from onset of labour to within 42 days post partum.Cause of maternal death.

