#### Additional descriptors

Descriptors of the dataset population as listed below will be collected and compared:

Maternal age at booking.Parity at booking.Ethnicity.Smoking at booking.Index of Multiple Deprivation for maternal home at the time of childbirth.Number of fetuses (seen at dating ultrasound scan).Birth order.Baby’s sex.

The occurrence of an adverse event as a result of participation within this trial is not expected, and no adverse event data will be collected.

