#### Detailed data collection of testing groups

For determining the process outcomes, individual-level data, not reported in the routine data sources, are required. To collect data on all women would negate the advantages of routine data use, so detailed data collection will be undertaken for a small subset of women at each site.

This will be retrospective source data collection using an online proforma designed for each testing strategy. At each site, individual data for a consecutive sample of at least 100 women per site, at gestational age ≥32 weeks, excluding women admitted for elective caesarean births, will be gathered. This will commence approximately halfway through the site’s data collection period.

This data will be extracted from the women’s healthcare records and transcribed by the research midwife at each site onto the GBS3-specific online database, using the NHS number, postcode and date of birth as the identifiers.

The detailed data collection will provide individual-level data associated with the testing coverage, IAP and resource use for approximately 4000 women in the risk factor-based usual care sites, 2000 women in ECM sites and 2000 women in the rapid testing sites.

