### Routine data sources

Data sharing agreements between the sponsor and data provider will enable the University of Nottingham to receive routine data for the GBS3 Trial from various sources (table 1). Routine data and the detailed dataset will be safely stored in an accredited Trusted Research Environment (Data flow charts online supplemental appendices 4A–C).

**Table 1 T1:** Routine data sources for GBS3 Trial

Data source	Description and use for GBS-3 trial
English Maternity Services Dataset (MSDS version 2) Maternity Services Data Set (MSDS) - NHS Digital and NHS Wales Informatics Service	These are patient-level datasets that capture key information at each stage of the maternity care pathway including the mother’s demographics, booking appointments, admissions and readmissions, screening tests, labour and delivery along with the baby’s demographics, admissions, diagnoses and screening tests. These will provide maternal secondary outcomes and other descriptive details.
UK Health Security Agency UK Health Security Agency - GOV.UK (www.gov.uk), Health Protection Wales Health Protection - Public Health Wales (nhs.wales)	Confirmed cases of all-cause early and late-onset neonatal sepsis and maternal sepsis identified through positive culture of a pathogenic bacteria.
National Neonatal Research Database Neonatal Data Analysis Unit | Faculty of Medicine | Imperial College London	Information on clinically suspected (negative or unknown culture status with ≥3 agreed clinical signs/symptoms, treated with antibiotics ≥5 days, within 7 days of birth) all-cause early neonatal sepsis, other secondary neonatal outcomes. All participating sites contribute data to this dataset.
Badgernet (Maternity)	Available as either a brief clinical summary record or a complete electronic health record system that captures all aspects of care and outcomes from booking to discharge from postnatal care. The latter system is used by more than 25% of English units. Data from the system would enable babies not ill enough to be admitted to a neonatal unit, and who remain on the postnatal ward, to be added to the trial dataset.
Badgernet (Neonatal)	This is the main source of the NNRD, along with additional variables which can add richer data for the primary outcome adjudication

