Paediatric Intensive Care Audit Network Database	An audit database recording individual details of the diagnosis and treatment of all critically ill babies in paediatric intensive care units. This will identify newborns not admitted to the neonatal unit or discharged and later readmitted to hospital (within 7 days of birth) with sepsis
Hospital Episode Statistics (England) and NHS Wales Informatics Service.	These contain details of all admissions, outpatient appointments and accident and emergency attendances at NHS hospitals in England and Wales, respectively.
Office for National Statistics	This will capture neonatal deaths and maternal deaths that happen at home and were not reported to a hospital.

GBS, group B streptococcus; NHS, National Health Service.

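### Blood-culture-confirmed maternal sepsis is confined to a subset of about 8,000 women, although Table 1 lists a routine source for it

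*Protocol article*

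**What the plan says.** The section on secondary clinical outcomes sets the general rule and two exceptions: "With the exception of maternal intrapartum anaphylaxis and systemic infection, all neonatal and maternal outcomes will be collected from routine data sources". The maternal list then limits the infection outcome: "In a subset of participants for whom detailed data is collected, systemic infection confirmed with a positive blood culture or suspected maternal sepsis", counted from labour onset to 42 days after birth. Culture-confirmed and suspected cases therefore form one outcome, observed only in the subset.

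The section on detailed data collection gives the size of that subset: "approximately 4000 women in the risk factor-based usual care sites, 2000 women in ECM sites and 2000 women in the rapid testing sites". It requires a gestation of at least 32 weeks and leaves out women admitted for elective caesarean. The process outcomes section describes the same sample but applies the caesarean exclusion at rapid test sites only.

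In Table 1, the row for the UK Health Security Agency and Health Protection Wales reads: "Confirmed cases of all-cause early and late-onset neonatal sepsis and maternal sepsis identified through positive culture of a pathogenic bacteria". That row mentions no subset.

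**The concern.** For culture-confirmed maternal sepsis, the outcome definition says the data do not come from routine sources, and the data-source table says that such data are obtained. Either Table 1 lists data that serve no stated outcome, or the outcome definition sets aside 97.5% of the denominator for an event the trial can already identify.

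This matters because confirmed bloodstream infection in mothers is likely to be uncommon. A comparison in about 4,000 against 4,000 women would then rest on a handful of events, and a null result would say little about either an increase or a decrease. The subset is also selected. It omits births before 32 weeks and elective caesareans, at all sites or at rapid test sites only, depending on which section governs. In the second case the denominator would differ between the randomised groups. The whole dataset takes all births from 24 weeks whatever the mode of birth, so it does not have this problem.

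**Working it through.** **Inputs from the article.** Sample size section: event rates 0.000986 and 0.0005916, power 90%, two-sided 5%, unclustered total 212,960, ICC 0.0001, mean cluster size 4,500, CV 0.31, final total 320,000. Detailed data collection section: about 4,000 women per randomised group.

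**Assumed.** Control-group rate of culture-positive maternal sepsis of 0.5, 1 or 2 per 1000. The article gives no rate.

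**Step 1: reproduce the plan's own figure.** Per group, n = [z(0.975)·√(2p̄(1−p̄)) + z(0.90)·√(p₁(1−p₁) + p₂(1−p₂))]² / (p₁−p₂)². With the stated rates this gives 106,481 per group, 212,962 in total, against 212,960 stated. Design effect = 1 + [(1 + 0.31²) × 4,500 − 1] × 0.0001 = 1.493, and 212,960 × 1.493 ≈ 317,980, against 320,000 stated. The same formula can therefore be used for the maternal outcome.

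**Step 2: share of women observed.** 8,000 / 320,000 = 2.5%, so 97.5% are not used.

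**Step 3: expected events if both groups share the assumed rate.** Subset: 8,000 × 0.0005 to 0.002 = 4 to 16. Full dataset: 320,000 × 0.0005 to 0.002 = 160 to 640.

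**Step 4: relative risk detectable at 80% power.** Power = Φ{[|p₁−p₂|·√n − 1.96·√(2p̄(1−p̄))] / √(p₁(1−p₁) + p₂(1−p₂))}, solved for p₂/p₁ > 1. The effective full sample is 212,960 / 2 = 106,480 per group.

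| Assumed control rate | Subset, 4,000 per group | Full data, effective 106,480 per group | Full data, 160,000 per group, clustering ignored |
|---|---|---|---|
| 0.5 per 1000 | 6.4 | 1.62 | 1.49 |
| 1 per 1000 | 4.2 | 1.42 | 1.34 |
| 2 per 1000 | 3.0 | 1.29 | 1.23 |

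At 1 per 1000, power for a relative risk of 1.5 is 9% in the subset and 90% at the effective full sample size. A relative risk of 0.6 gives the same two figures, so the result does not depend on direction.

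**Step 5: clustering within the subset.** With 100 women per site and the protocol's ICC, the design effect is 1 + 99 × 0.0001 = 1.0099, and 8,000 / 1.0099 ≈ 7,922. Ignoring clustering in the subset column makes almost no difference.

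**Step 6: if the outcome is more common.** In the subset, power for a relative risk of 2 is 37% at 2 per 1000, 74% at 5 per 1000 and 96% at 10 per 1000. For a relative risk of 1.5 it is 29% at 5 per 1000 and 52% at 10 per 1000.

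**The case against.** The subset outcome also counts suspected sepsis, which may be a good deal more common than confirmed bloodstream infection. Step 6 shows that at 5 to 10 per 1000 the subset has fair power for a doubling. That stands: the subset is useful for the combined or suspected outcome. It does not explain why the rarer confirmed component should be limited in the same way when a source for it is listed.

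The article is condensed, and the full protocol may explain the split. Leaving out detail would be no finding, but here two explicit statements disagree. It is also true that the Table 1 row gives neither specimen type nor date window for mothers, so that source may not match the outcome exactly. That bears on the cost of the change.

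Two stronger readings are tempting. A reader might infer that anaphylaxis is also confined to the subset while routine data could supply it for all women. The documents do not support this. The item "Maternal intrapartum anaphylaxis due to IAP" has no subset qualifier, and all that is said of its source is that it is not routine data. No Table 1 row names it. The admissions row says only "These contain details of all admissions, outpatient appointments and accident and emergency attendances at NHS hospitals", and coded admissions might not attribute a reaction to prophylaxis.

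A reader might also conclude that the maternal harm question cannot be answered, especially given "no adverse event data will be collected". That goes too far. Maternal death, its cause, mode of birth and hospital stay remain routine-data outcomes on all women. The quoted statement concerns events arising from trial participation and does not cancel the listed anaphylaxis outcome. Nor does the introduction list maternal infection among the complications of antibiotics, so sepsis here is a clinical outcome that could move either way.

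**Conclusion.** The point holds for culture-positive maternal sepsis. The outcome definition and Table 1 contradict each other, and following the definition as written would use 2.5% of the women. At assumed rates of 0.5 to 2 per 1000, the detectable relative risk is 6.4 to 3.0 in the subset, against 1.62 to 1.29 in the full dataset at the protocol's effective sample size.

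These figures rest on the assumed rates and on the routine source covering essentially the whole dataset, apart from opt-outs. They also rest on the ICC of 0.0001, which was chosen for neonatal infection; a larger ICC for maternal sepsis would narrow the gain. Nothing here touches the primary outcome, its power or its analysis. The weight is moderate.

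**What to change.** Bring the outcome definition into line with Table 1 before analysis:

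- Define blood-culture-positive maternal sepsis, from labour onset to 42 days, as a secondary outcome on the whole dataset, taken from the UK Health Security Agency and Health Protection Wales linkage.
- Keep suspected maternal sepsis as a separate outcome in the detailed-data subset.
- Amend the opening sentence on secondary clinical outcomes so that only suspected sepsis remains in the systemic infection exception; the anaphylaxis exception is untouched by this point.
- State one rule for elective caesareans in the subset, since the two sections that describe it differ.

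The cost is that the combined outcome becomes two. The laboratory records must be linked to mothers as well as babies, with a date window and a restriction to blood cultures. No new data provider is named and no further collection at sites is needed, which matters because site data collection ended on 31 March 2024. If the agreed linkage turns out not to supply mothers' cultures over that window, the Table 1 row should be corrected and the limited precision of the subset outcome stated.
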